#### 16.1.2 Baseline assessment

A baseline assessment will be conducted for each participant comprising demographic information, socioeconomic information, insecticide treated net (ITN) and indoor residual spraying use, medical and obstetric history, and clinical assessment. Any relevant information already collected during the screening process or at previous antenatal appointments for the same pregnancy will be copied from the antenatal cards onto the CRF, so that questions, tests and examinations are not unnecessarily duplicated.

Study-relevant information recorded at the first visit will include age; area of residence; prior use of ITNs; number of previous known pregnancies and number of previous births. Clinical assessment will include height and weight, fundal height, reported date of last menstrual period and estimated gestation.

A 5 ml venous blood sample will be taken and used for both routine and study-specific testing. This will be obtained after consent for eligibility screening has been obtained but before consent for enrolment in the trial; women who have not been tested for HIV in their current pregnancy will be tested for HIV, and all women will be tested for anaemia and haemoglobin levels. Women not previously tested for syphilis in this pregnancy will be tested and treated if positive. The same blood sample will be prepared for later study-specific testing for malaria (blood smear microscopy and PCR), for markers of immunity to *P. falciparum* malaria, and for markers of iron deficiency. Aliquots of separated blood plasma will be stored at -20 or -80C for immunity studies. A filter-paper sample will be prepared and stored for future research if the woman has given her consent for this.

If not already done, an ultrasound scan will be done at this visit or at a separate visit within a month of enrolment.

#### 16.1.3 Study intervention

The first dose of IPTp-SP or RDT screening for ISTp-DP will be administered to asymptomatic women at this visit as described in section 15.1. If women have symptomatic malaria they will be treated as described in section 15.2.

#### **16.1.4 Routine antenatal care and treatment of illness**

Routine antenatal care and treatment of any illness identified at this visit will be provided as described in section 15.2. This will include the provision of a suitable ITN if the woman does not already have one, and advice on sleeping under the net for the duration of the pregnancy.

#### **16.1.5 Recording of morbidity and medication taken**

All participants will be asked about any symptoms or illnesses they have had in the last month, and any medication taken.

### **16.2 Interim visit**

A second clinic visit will be scheduled between four and eight weeks after the first visit.

#### **16.2.1 Study intervention**

The second dose of IPTp-SP or RDT screening for ISTp-DP will be administered to asymptomatic women at this visit as described in section 15.1. If women have symptomatic malaria they will be treated as described in section 15.2.

#### **16.2.2 Routine antenatal care and treatment of illness**

Routine antenatal care and treatment of any illness identified at this visit will be provided as described in section 15.2.

#### **16.2.3 Recording of morbidity and medication**

Participants will be asked about any symptoms or illnesses they have had since the first antenatal visit of the study, and any medication taken.

### **16.3 Additional interim visit**

This is an additional visit only for participants who were enrolled in the trial at between 16 and 23 weeks gestation and for whom four doses of the study intervention can be provided at intervals of four to eight weeks apart, with the final visit at 34 to 37 weeks. This visit will be conducted in the same way as the other interim visit.

### **16.4 Final antenatal visit**

A clinic visit will be scheduled between 34 and 37 weeks gestation, at least four weeks after the previous visit.

#### **16.4.1 Study intervention**

The third or fourth dose of IPTp-SP or RDT screening for ISTp-DP will be administered at this last scheduled visit as described in section 15.1. If women have symptomatic malaria they will be treated as described in section 15.2

#### **16.4.2 Routine antenatal care and treatment of illness**

Routine antenatal care and treatment of any illness identified at this visit will be provided as described in section 15.2.

As part of routine care, all women will have their haemoglobin levels tested at point of care. Women found to be anaemic ( $Hb \leq 11 \mu g/L$ ) will be treated as appropriate. All women will also be re-tested for HIV, as recommended in the latest WHO guidelines. This will be obtained for a single venous blood draw with additional study-specific testing as described in section 16.4.4.

#### **16.4.3 Recording of morbidity and medication**

Participants will be asked about any symptoms or illnesses they have had since the first antenatal visit of the study, and any medication taken.

#### **16.4.4 Additional study-specific testing**

All consenting participants will have venous blood samples taken, prepared and stored for later malaria testing using standard microscopy of blood smears and PCR of dried blood spots. Testing will be done blindly and results will not be made available to study staff until the end of the trial.

### **16.5 Home visits and telephone reminders (RDT-positive women treated with DHA-PQ only)**

Participants who receive DHA-PQ treatment as part of ISTp and who have a mobile or home telephone number will be telephoned on days two and three after the first dose to remind them to take the second and third doses, and will otherwise be visited at home to ensure compliance.

All participants who receive DHA-PQ treatment as part of ISTp will be visited at home day three after receiving their first dose of DHA-PQ at the clinic.

At this visit, participants will be asked whether they have taken the tablets assigned for the previous day and the current day. If they have not taken the tablets, they will be asked for their reasons, and if willing, will be encouraged to take the remaining tablets during the visit. They will also be asked about any symptoms they have experienced on the day of the visit and two previous days. If the symptoms are serious adverse events, a 2 ml venous blood sample will be taken to measure blood drug levels.

Any cases of non-adherence to the study medication and the reasons given for will be recorded in the CRF.

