### 7.2.2 Study of efficacy versus effectiveness

This trial is designed primarily to assess the efficacy of ISTp when implemented as intended. This proof of concept is needed as a logical step before further assessments of effectiveness in practice are undertaken, as it has not yet been established in this context. In addition, as any effect will usually tend to be greater under conditions of optimal implementation, the sample size required is smaller for an efficacy trial than for an effectiveness trial. Therefore efforts will be made to maximise participant adherence to the study protocol, including telephone reminders to women to take their DHA-PQ as prescribed, and active follow-up of participants who miss scheduled appointments.

However, some attempts will be made to assess the potential effectiveness of ISTp in practice. Data will be collected to assess the tolerability of the intervention and levels of adherence under the trial conditions.

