### 9.2.3 Tolerability outcomes

1. Non-serious adverse events in the mothers
2. Adherence to study medication

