### 15.1.1 Administration of the study drugs

Women in either group who attend for a scheduled study appointment with fever and malaria confirmed by RDT or microscopy will be treated for malaria. In the case of women in the IPTp-SP group, case-management treatment will be given in place of the scheduled dose of SP, and this will be recorded on the CRF.

RDTs will be performed according to the manufacturer's instructions by the study staff at the clinic. Women in the ISTp group testing positive for either *P. falciparum* or other malaria species will be treated with DHA-PQ.

Participants receiving single-dose SP or the first dose of DHA-PQ will be given some clean water for swallowing the tablets. They will be observed swallowing the tablets and for thirty minutes afterwards. If vomiting occurs during this time the full dose will be repeated. If the participant vomits again after the repeated dose she will be discontinued from the trial and provided with second line therapy for malaria (CoArtem).

Participants receiving treatment with DHA-PQ will be given the remaining doses to take home, with instructions to take half the tablets the following day and half tablets the day after. Women with mobile or home telephones will be telephoned the next day to remind them to take their next dose. Women without mobile phone will be visited at home. All women regardless of mobile phone ownership will be visited by a fieldworker on the second day to check whether they have taken the tablets and whether they have had any problems.

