## 17.3 Analysis

### 17.3.1 Inclusion of participants in the analysis

Participants will be included in the modified intention-to-treat analysis if they satisfied all the entry criteria and received the study intervention (screening by RDT or dose of SP) on at least one occasion, with no other exclusions. Women who give consent to enter the study but withdraw the same day and did not receive any study intervention (RDT or SP) will be classed as screening failures and not included in the analysis (e.g. in ongoing trials a few women gave consent, but then changed their mind during the same visit prior to, or during the study enrolment procedures).

Participants will be included in the per-protocol analysis if they satisfied all the entry criteria and either received the study intervention (IPTp-SP or ISTp-DP) on at least three separate occasions at least four weeks apart; or reached a study end-point before completion of the three-visit schedule but received the intervention at least once; or received an approved alternative treatment for symptomatic malaria according to protocol that replaced the need for the scheduled intervention. Participants who received the study medication but were reported not to have adhered to treatment (defined as taking at least 2/3 of the recommended dose over the recommended time period, on each occasion that treatment is required) or who used prohibited medication will be excluded from the per-protocol analysis. Women who were HIV negative at enrolment but HIV positive by the third trimester will be excluded from the per-protocol analysis.

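### Adherence to the home doses of DHA-PQ is taken from the woman's answer with no tablet count, so the adherence outcome may be too high and a few under-dosed women may stay in the per-protocol set

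*Combined protocol and SAP*

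**What the plan says.** DHA-PQ is a three-day course. Section 15.1.1 has the first dose taken at the clinic: "They will be observed swallowing the tablets and for thirty minutes afterwards". The rest is unobserved: "Participants receiving treatment with DHA-PQ will be given the remaining doses to take home".

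Every treated woman is then seen at home. Section 15.1.1 says she is "visited by a fieldworker on the second day to check whether they have taken the tablets", without saying how the check is made. Section 16.5 gives the method: "participants will be asked whether they have taken the tablets assigned for the previous day and the current day". If she has not, she is asked why and encouraged to take what is left during the visit, and non-adherence with its reasons goes on the CRF. The visit table in 3.2 marks adherence monitoring only at the telephone call and the home visit.

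The answer is used in three places:
- Section 9.2.3 lists "Adherence to study medication" as an outcome and gives no definition.
- Section 17.3.1 removes from the per-protocol set women who were "reported not to have adhered to treatment (defined as taking at least 2/3 of the recommended dose over the recommended time period", judged on each treatment occasion.
- Section 7.2.2, on how ISTp might work in practice, says: "Data will be collected to assess the tolerability of the intervention and levels of adherence under the trial conditions".

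**The concern.** A woman asked at home by the study team, after reminders to take her tablets, has some reason to say that she took doses she missed and little reason to say the opposite. Error in her answer is therefore more likely to raise reported adherence than to lower it. The tablets themselves are in the house and the number dispensed is known, yet the plan does not ask the visitor to count them.

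Two results depend on her answer. One is the adherence outcome. The other is the per-protocol set, since exclusion applies to women who "were reported not to have adhered to treatment". Section 17.3.3 gives that set a role beyond a sensitivity check: if superiority is not shown, the 15% non-inferiority margin is assessed in it as well as in the intention-to-treat population. SP is a single observed dose, so error from unobserved study doses can arise in the ISTp arm only.

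**Working it through.** **Number of women concerned.** Section 7.2.11 puts about 776 women in the ISTp arm and expects 20% to 30% to be treated. 776 x 0.20 = 155.2 and 776 x 0.30 = 232.8, which reproduces the stated 155 to 233. (Half of the 1655 in section 17.1 would be 827.5, giving 165.5 to 248.25 treated; the results below would hardly change.)

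**Adherence outcome.** The documents give neither a true adherence rate nor a misreporting rate. Both are assumptions here: true adherence a of 80% to 90%, and a share m of 25% to 50% of non-adherent women who say that they adhered.

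Reported adherence = a + (1 - a) x m. Women misclassified = N x (1 - a) x m.

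| a | m | Reported | Overstatement | Misclassified, N = 155 | Misclassified, N = 233 |
|---|---|---|---|---|---|
| 90% | 25% | 92.5% | 2.5 points | 3.9 | 5.8 |
| 90% | 50% | 95.0% | 5 points | 7.7 | 11.6 |
| 80% | 25% | 85.0% | 5 points | 7.7 | 11.6 |
| 80% | 50% | 90.0% | 10 points | 15.5 | 23.3 |

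For scale, the 95% confidence half-width, 1.96 x sqrt(p(1 - p)/N), is 4.7 points for p = 0.90 and N = 155, and 3.9 points for N = 233. The bias at the upper end is about twice the sampling error. At the lower end (p = 0.925, half-width 4.1 or 3.4 points) it is smaller than the sampling error.

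**Per-protocol set.** With equal daily doses:
- Observed clinic dose only: 1/3 of the course.
- Clinic dose plus one home dose: 2/3, which meets the rule.
- Tablets swallowed during the visit have been received and count.

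A woman is wrongly kept only if she took less than one full home dose in total, including anything taken at the visit, and said otherwise. That is a subset of the women in the table.

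A ceiling follows from treating every misreporting woman as below 2/3. The undetected share of treated women is then at most 0.20 x 0.50 = 0.10, and the share of the ISTp arm at most 0.30 x 0.10 = 0.03. Of the 491 per arm planned for first and second pregnancies (section 17.1), that is 491 x 0.03 = 14.7 women.
- If these women carry the control risk and the others keep the planned risk: 0.97 x 0.302 + 0.03 x 0.403 = 0.305, so RR = 0.305/0.403 = 0.757 against the planned 0.75.
- If the whole ISTp benefit runs through treated women: 0.302 + 0.10 x (0.403 - 0.302) = 0.3121, so RR = 0.774.

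**Primary result.** Section 17.3.3 makes the modified intention-to-treat analysis primary, and 17.3.1 admits women to it regardless of adherence. The effect there is nil.

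**The case against.** Several points on the other side are sound:

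- **Admitted misses are captured.** Section 16.5 asks first, takes the reason, and only then encourages the woman to take the rest, with non-adherence recorded. A reader might infer that prompting at the visit hides missed doses. For women who admit the miss, the sequence does not support that. What is not required is a record of how many tablets were swallowed before the visit and how many during it.
- **An objective measure exists.** Section 16.6 takes a blood drug level 14 days after the first dose, and 20.3 requires dispensing and return records. Neither is linked to the adherence outcome or to per-protocol membership, no threshold is given, and return records cannot show what happened to tablets that stayed at home.
- **Silence is not refusal.** A count might be described in operating procedures that are not public. The protocol sets out the content of the visit in some detail, however, and gives asking as the method.
- **The claim is modest.** Section 7.2.2 describes an efficacy trial with reminders and promises adherence under trial conditions, not unsupervised adherence. A count at the same visit would also follow reminders.
- **A naive count can mislead.** The question covers the current day's dose, which may not yet be due, so a plain count could score a woman on schedule as non-adherent.

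The last two points shape the fix. None of the five supplies a method for the two unobserved doses other than the woman's word.

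**Conclusion.** The plan measures adherence to two of the three daily doses by self-report, although a better measure is available at a visit already made to every treated woman. The adherence figure may therefore be too high. On the stated assumptions the excess is 2.5 to 10 points, with about 4 to 23 women misclassified. The documents do not allow the stronger statement that the figure is overstated, because they give no misreporting rate.

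A reader might also infer that the same 4 to 23 women would wrongly remain in the per-protocol set. That does not follow: a woman who misses one home dose still meets the two-thirds rule, and prompting at the visit can bring others up to it. The number wrongly kept is smaller and unknown, and confined to the ISTp arm. If under-dosed women do worse, keeping them raises the ISTp risk, which works against the new strategy and does not favour a finding of non-inferiority. That direction is not assured, since adherence is not randomised.

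This is a cheap improvement to one tolerability outcome and one secondary analysis set, with no bearing on the primary result. It is worth making before enrolment because the tablets cannot be counted afterwards.

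**What to change.** In 16.5 and the CRF, have the fieldworker record the date and time of the visit and count the remaining tablets before asking or prompting. Record separately any tablets swallowed during the visit. Then define two measures:

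- **Outcome in 9.2.3:** adherence before the visit, under trial conditions, as tablets taken divided by tablets due by that time, with the observed clinic dose in both numerator and denominator.
- **Two-thirds rule in 17.3.1:** total tablets taken (clinic, home and at the visit) divided by the total prescribed course. Reword the sentence so that the definition attaches to adherence.

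Keep the woman's own report and her reasons as supporting data, and say whether the day-14 drug level is also supporting.

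The timing of the visit has to be reconciled, because it decides which tablets were due. Sections 7.1, 15.1.1 and 17.3.4 put it on day two; sections 7.2.11 and 16.5 put it on day three. This may only be a difference in how days are numbered, but the text does not say. A dose due after the visit would still rest on self-report.

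The cost is about a minute per visit and a few CRF fields. The adherence figure may turn out less favourable, and tablets thrown away will still be counted as taken.

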| Form                     | Co-formulated tablets: 40 mg dihydroartemisinin and 320 mg piperaquine                                                                                                                                                                                                                                                                                                                                                                                                                                                                                                               |
| Dose                     | 2 mg dihydroartemisinin and 16 mg piperaquine per kg body weight per day for three days                                                                                                                                                                                                                                                                                                                                                                                                                                                                                              |
| Route                    | Oral, with water                                                                                                                                                                                                                                                                                                                                                                                                                                                                                                                                                                     |

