## 15 Treatment of trial participants

### 15.1 The study intervention

Participants will receive one of the following two interventions during the second and third trimesters of pregnancy; provided at each of three scheduled visits between four and six weeks apart.

**IPTp-SP Group:** Treatment with a three tablets of sulphadoxine-pyrimethamine, each containing sulphadoxine (500 mg) and pyrimethamine (25 mg). This is the standard and only

drug of choice for IPTp in Africa. SP will be purchased from Durbin PLC in the UK and will be manufactured according to the GMP: Durbin PLC is a UK registered company - Company Registration Number: 3626868; Head Office: [name] T: [name], F: [name], [contact]

**ISTp-DP Group:** Screening for malaria using a combined HRP-2/ pLDH (*P. falciparum*/ pan-malaria) rapid diagnostic test (First Response® Malaria pLDH/HRP2 Combo Test, target antigen pLDH (pan); HRP2; Premier Medical Corporation Ltd, USA), and treatment if RDT-positive with dihydroartemisinin-piperaquine (Sigma Tau). Each tablet will contain 40 mg dihydroartemisinin and 320 mg piperaquine. Treatment will be given for three days, with the daily number of tablets depending on the weight of the woman to the nearest half tablet; dosage being 2 mg/kg/day of dihydroartemisinin and 16 mg/kg/day piperaquine.

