### **18.2 Reporting procedures for all adverse events**

An independent physician will be appointed by the sponsor (LSTM) to act as a study safety monitor. He or she will be based in Malawi.

All adverse events occurring during the study, observed by the investigator or reported by the participant, whether or not attributed to study medication, will be recorded using Adverse Event Forms. The following information will be recorded: description, date of onset and end date, severity, seriousness and action taken. Follow-up information will be provided as necessary.

The intensity of events will be assessed on the following scale: 1 = mild, 2 = moderate, 3 = severe, 4 = life-threatening, 5 = death

The relationship of adverse events to the study medication will be assessed by a medically qualified investigator and the independent safety monitor. If the safety monitor disagrees with the investigator's assessment, both opinions will be included in the report.

The safety monitor will evaluate the expectedness of each suspected adverse event according to the Summary of Product Characteristics for SP and the Investigators Brochure for DHA-PQ.

Any adverse reactions to the study drugs will be followed-up until resolution or stabilisation to ascertain the final outcome.

The investigator will judge whether or not an adverse event is of sufficient severity to require discontinuation of the study treatment. If this occurs, or if the participant herself wishes to withdraw due to what she considers to be an intolerable adverse reaction, she will be offered an end of study assessment and be given appropriate medical care until symptoms cease or the condition becomes stable. If she agrees she will be continued to be followed up according to schedule.

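### Read literally, the section 16.5 home-visit instruction conflicts with the stated daily DHA-PQ dose when both take-home days were missed, and section 17.3.1 does not say how such an intake is classified

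*Combined protocol and SAP*

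**What the plan says.** All references are to the combined protocol and SAP.

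- **Dose.** The synopsis (section 3) gives "2 mg dihydroartemisinin and 16 mg piperaquine per kg body weight per day for three days". Section 15.1 repeats it: "Treatment will be given for three days", with "dosage being 2 mg/kg/day of dihydroartemisinin and 16 mg/kg/day piperaquine". On strength: "Each tablet will contain 40 mg dihydroartemisinin and 320 mg piperaquine".
- **Split of the course.** Under section 15.1.1 the first dose is swallowed under observation at the clinic. The woman goes home with the rest and with "instructions to take half the tablets the following day and half tablets the day after".
- **Home visit.** Section 16.5 has the visitor ask about two days' tablets, those for the day before and those for the day of the visit. If they were not taken, the woman is asked why and, "if willing, will be encouraged to take the remaining tablets during the visit". Symptoms on the visit day and the two days before it are then asked about. Non-adherence and the reasons for it go on the CRF.
- **Adherence rule.** Section 17.3.1 excludes non-adherent women from the per-protocol set. The definition in brackets, "defined as taking at least 2/3 of the recommended dose over the recommended time period", describes adherence although it follows the words for non-adherence. It applies on each occasion that treatment is needed.

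**The concern.** The visitor's question covers two days, so the protocol foresees that both may have been missed. In that case the tablets still in the house are two daily doses, and nothing in section 16.5 or elsewhere limits the prompt to one day's tablets. A fieldworker who follows section 16.5 as written would then depart from sections 3, 15.1 and 15.1.1.

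Two things are at stake. First, it is a staff instruction on an investigational product in pregnant women, and section 7.2.11 itself says that its safety in pregnancy has been less studied. Such an instruction should not contradict the protocol's own dosing. Second, the plan does not say whether a woman who catches up in this way counts as adherent, so two analysts could build different per-protocol sets from the same data.

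**Working it through.** **Inputs.** Daily dose 2 mg/kg dihydroartemisinin and 16 mg/kg piperaquine, three daily doses, tablets of 40 mg/320 mg rounded to the nearest half (sections 3 and 15.1); two equal take-home parts (15.1.1); threshold 2/3 (17.3.1). The documents give no body weights, so 40 to 70 kg is an assumption for illustration.

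**Step 1: do the dose and tablet agree?** 2/40 = 0.05 and 16/320 = 0.05 tablet per kg per day. They agree, so the stated dose is coherent in itself.

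**Step 2: what remains if both take-home days were missed?** Two daily doses: 2 × 2 = 4 mg/kg dihydroartemisinin and 2 × 16 = 32 mg/kg piperaquine.

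| Weight (assumed) | Tablets per day (0.05 × kg) | Tablets remaining | Piperaquine at once (tablets × 320 mg) |
|---|---|---|---|
| 40 kg | 2 | 4 | 1,280 mg |
| 50 kg | 2.5 | 5 | 1,600 mg |
| 60 kg | 3 | 6 | 1,920 mg |
| 70 kg | 3.5 | 7 | 2,240 mg |

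For weights between these, rounding shifts the mg/kg figure slightly. The amount is still exactly twice the woman's own daily allocation at any weight.

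**Step 3: when does the conflict arise?** If only the visit day's tablets remain, they are one daily dose (2 and 16 mg/kg), taken on the assigned day, and the sections agree. The double amount in one sitting needs both days' tablets to be untaken.

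**Step 4: what happens to the adherence fraction?**

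| Situation | Fraction of course | Meets 2/3? |
|---|---|---|
| Clinic dose only | 1/3 | No |
| Clinic dose and one take-home day | 2/3 | Yes |
| Clinic dose and both days' tablets at the visit | 3/3 | Yes, if within the recommended period |

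So the visit can move a woman across the threshold only if both days had been missed, which is the same case that produces the conflict.

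**Step 5: does the visit fall within the recommended period?** The labels differ. Section 3.2 puts both the call and the home visit at plus two days. Section 7.1 puts the home visit on day two after the first dose. Section 15.1.1 has the call the next day and the home visit on the second day. Section 16.5 has calls on days two and three after the first dose and the visit on day three after it. The questions asked at the visit (that day's tablets, and symptoms over that day and the two before) point to the third treatment day, inside the course. A literal three days after the first dose would be one day outside it, and a catch-up then might not satisfy the time condition in section 17.3.1.

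**The case against.** The strongest reply is that this is a wording gap in a sub-case. Section 16.5 says that the woman is encouraged, and only if willing. The first dose is observed, and a call or a home visit follows the next day, so few women may arrive with both days untaken. All of that stands, and it limits how often the conflict arises. It does not remove it, because no passage limits the prompt to one day's tablets.

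Several stronger inferences are tempting, and the documents do not support them:

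- *That a woman who stopped because she felt ill is urged on before anyone asks why.* Section 16.5 has her reasons asked first. Section 18.2 says "The investigator will judge whether or not an adverse event is of sufficient severity to require discontinuation of the study treatment", but it sets no order of steps at a home visit.
- *That later effects go unasked.* Sections 16.2.3 and 16.4.3 ask about symptoms at later visits, the table in section 3.2 marks tolerability there, and women are asked back on day 14 for blood tests (section 16.6). The early self-report does precede the effects of tablets taken at the visit, but this is so for any third dose taken then.
- *That the missed doses leave no trace.* Section 16.5 requires non-adherence and its reasons on the CRF. What it does not require is the number of tablets taken on each day.
- *That the plan counts her as fully adherent.* There is no such category. Section 17.3.1 is silent on caught-up intake, which is a gap and not a rule.
- *That the differing reminder labels cause missed doses.* This is conjecture. If the clinic day is counted as day one, the calls on days two and three fit with a call the next day.

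**Conclusion.** The contradiction stands. For a woman who has taken neither take-home dose, section 16.5 read literally leads to 4 mg/kg dihydroartemisinin and 32 mg/kg piperaquine in one sitting, against 2 and 16 mg/kg per day in sections 3 and 15.1 and the two-day split in section 15.1.1. I take no view on which passage is right. The doubling follows from the documents alone; only the body weights in the tablet table are assumed.

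How many women this concerns cannot be derived. Section 7.2.11 expects 155 to 233 women to receive DHA-PQ (20% to 30% of 776), but no rate of missing both days is given. A reader might try 5% to 15%, which gives 8 to 35 women (155 × 0.05 = 7.75; 233 × 0.15 = 34.95, one course each). That rate has no basis in the documents and the conclusion does not rest on it. Nor do they state a safety limit for a single sitting, so the size of any harm cannot be inferred from them.

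The statistical consequence is confined to the per-protocol set and the descriptive adherence outcome. The primary modified intention-to-treat analysis is unaffected. Even so, a staff instruction that can contradict the protocol's own dosing of the investigational product should be reconciled before it is used.

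**What to change.** 1. Reconcile section 16.5 with sections 3, 15.1 and 15.1.1 for the case in which more than one day's tablets remain at the visit. The sponsor's medical lead should decide the content.
2. Use one day-numbering convention, and align the visit-day and reminder-day labels in sections 3.2, 7.1, 15.1.1 and 16.5.
3. Record on the CRF the number of tablets taken on each calendar day of the course.
4. State in section 17.3.1 how a caught-up intake is classified for the adherence outcome and the per-protocol set, and what the recommended period is in days. Reword the sentence so that the bracketed definition is clearly that of adherence.

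The cost is protocol wording and one CRF line. No visits, staff or sample size change.
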